### Statistics

The effect of the intervention on the primary and secondary outcomes will be performed using a multi-level mixed model or generalized linear mixed models (GLMM) based on comparison between the intervention and the control group from baseline (T0) to 12 months after baseline (T1). Four levels will be included in the mixed model: time (measurement time points), worker, working team and enterprise. The multi-level analyses will concurrently take into account the clustering of observations of workers within the working team, as well as repeated measurements within each worker. Sensitivity analyses will be conducted under different assumptions about missing data [68].

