**Methods/Design:**

A two-year cluster randomized controlled design will be utilized, in which controls will also receive the intervention in year two. More than 400 workers from three companies in Denmark will be aimed to be cluster randomized into intervention and control groups with at least 200 workers (at least 9 work teams) in each group. An organizational resources audit and subsequent action planning workshop will be carried out to map the existing resources and act upon initiatives not functioning as intended. Workshops will be conducted to train leaders and health and safety representatives in supporting and facilitating the intervention activities. Group and individual level participatory visual mapping sessions will be carried out allowing team members to discuss current physical and psychosocial work demands and resources, and develop action plans to minimize strain and if possible, optimize the resources. At all levels, the intervention will be integrated into the existing organization of work schedules. An extensive process and effect evaluation on need for recovery and work ability will be carried out via questionnaires, observations, interviews and organizational data assessed at several time points throughout the intervention period.

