### Randomization

The working teams will be randomized to either the intervention group or control group utilizing cluster level randomization. A randomized block design will be utilized to prevent contamination between participating adjoining team. Thus, the working teams will be structured in blocks based on their geographical proximity and common leaders. These blocks will then be randomized into either control or intervention groups using a computer generated randomization schedule. In the second phase of the intervention, the control group will also receive the intervention.

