### Intervention development and planning

Two steering groups will be established at each company. One is a strategic steering group consisting of a managerial group (often the managerial team) responsible for long term adaptation and evaluation of the usefulness of PIPPI, and the other is a project steering group responsible for monitoring and supporting the day to day activities of PIPPI. The steering group will manage the overall intervention process and ensure intervention progress at all levels of the organization throughout the project period. The steering group will (a) support data collection for effect and process evaluation, (b) discuss and monitor the screening process and developed action plans, (c) facilitate participation in intervention activities, (d) follow-up on progress, (e) reflect on the factors which will facilitate or hinder the progress of intervention, (f) discuss the evaluation of organizational resources and the corresponding action plan and (g) develop a communication strategy to ensure distribution of proper and timely information to the participating workers, managers and support systems.

The individual (I), group (G), leader (L), and organizational (O) levels of the workplace, referred to as IGLO [48], will be actively involved in the intervention activities. It signifies an approach that seeks to coordinate and integrate intervention activities at various levels of the organization. The aim of this approach is to achieve a thorough implementation and support throughout the organization. The specific intervention activities are listed below according to the level of the organization involved.

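### With only three companies, enter company as a fixed effect rather than a random model level, and state that blocks are randomised within company

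*Protocol article*

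**What the plan says.** **Number of companies.** The Abstract (Methods/Design) states: "More than 400 workers from three companies in Denmark will be aimed to be cluster randomized into intervention and control groups".

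**Model.** The Statistics section states: "Four levels will be included in the mixed model: time (measurement time points), worker, working team and enterprise". It does not say whether enterprise is random or fixed. Its next sentence says the analysis accounts for "clustering of observations of workers within the working team, as well as repeated measurements within each worker", and does not mention enterprise again. The effect is assessed on the period from T0 to T1.

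**Allocation.** The Randomization section says that "the working teams will be structured in blocks based on their geographical proximity and common leaders", and then: "These blocks will then be randomized into either control or intervention groups using a computer generated randomization schedule". It gives neither the number of blocks nor any role for company in the schedule.

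**Organisation.** Intervention development and planning says: "Two steering groups will be established at each company". Limitations and risks adds that the steering group is to keep the intervention teams' actions from reaching controls before the first follow-up.

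**The concern.** A company random effect is meant to carry what teams in the same company share. Three units give very little information on its variance. When the estimate is zero, the level has no effect on the analysis, whatever the companies have in common.

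That matters little if both arms are evenly present in every company, because company then drops out of the arm contrast. It matters if the split is uneven. A reorganisation or a company's own health programme during year one, in a company lying wholly in one arm, would move that arm alone. The article expects such events: its sample size section warns of organisational changes that could remove whole clusters. No rule in the article guarantees an even split by company.

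**Working it through.** **1. The plan's own figure.** Inputs from Sample size calculation: effect 0.50 SD, alpha 0.05 (two-sided assumed), power 0.90, ICC 0.05, 22 workers per team, 9 teams per arm.
- Design effect: 1 + (22 − 1) × 0.05 = 2.05. The article prints 1.54, which these inputs do not give; that is a separate matter.
- With 9 × 22 = 198 workers per arm, the noncentrality is 0.5 / √(2 × 2.05 / 198) = 3.47.
- On 2 × (9 − 1) = 16 df, the t-based power is 0.903. The stated 9 teams (200 workers) per arm is reproduced with 2.05.

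**2. Precision of a company variance.** Three companies give 2 df. The chi-square limits are 0.0506 and 7.38, so the 95% interval for the SD runs from √(2/7.38) = 0.52 to √(2/0.0506) = 6.3 times the estimate.

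**3. How often it is estimated at zero.** Assume 3 companies × 6 teams × 22 workers, team ICC 0.05 and company ICC c (assumed; it stands for company-specific change).
- Variance of a team mean: v = 0.05 + (0.95 − c)/22.
- The ANOVA estimate is zero or negative when F(2, 15) < x, with x = v/(v + 6c). Its probability is 1 − (1 + 2x/15)^(−7.5).

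| c | v | x | P(estimate ≤ 0) |
|---|---|---|---|
| 0 | 0.0932 | 1 | 60.9% |
| 0.01 | 0.0927 | 0.607 | 44.2% |
| 0.02 | 0.0923 | 0.435 | 34.5% |
| 0.05 | 0.0909 | 0.233 | 20.5% |

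**4. A company wholly in one arm, if allocation ignores company.** Let b be the number of blocks per company (assumed).
- Simple allocation, at least one such company: 1 − (1 − 2 × 0.5^b)³.
- Balanced overall split: count the allocations. For b = 2, 20 allocations put 3 of 6 blocks in intervention, and 2³ = 8 of them have both arms in every company, so 1 − 8/20 = 60%.
- Two companies wholly in opposite arms, balanced split: 6 × C(b, ⌊b/2⌋) / C(3b, ⌊3b/2⌋), for example 6 × 3/126 = 14% for b = 3.

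| b | At least one company, simple | At least one company, balanced | Two companies in opposite arms, balanced |
|---|---|---|---|
| 2 | 88% | 60% | 60% |
| 3 | 58% | 36% | 14% |
| 4 | 33% | 14% | 3.9% |
| 5 | 18% | 7% | 0.9% |
| 6 | 9% | 2.5% | 0.25% |

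Randomised within company, with both arms in each, every entry is zero.

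**5. Consequence of the unfavourable split.** Suppose one company is all intervention, one all control, and the third has 3 teams in each arm. All powers in this step use the normal approximation.
- Balanced reference: SE = √(2v/9) = 0.144, power about 0.94.
- Company fixed: only the third company informs the contrast. SE = √(2v/3) = 0.249, power about 0.52.
- Company random, variance known: power 0.85 to 0.69 for c from 0.01 to 0.05.
- Company term dropped (variance taken as zero): the true variance is 2v/9 + 2 × (6/9)² × c. For c = 0.05 that is 0.0202 + 0.0444 = 0.0646, SE 0.254, against an assumed SE of 0.142. The type I error is then 0.27; for c = 0.01 it is 0.10.

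**6. Cost of the fix.** With company fixed and arms balanced in each company, residual df are 18 − 3 − 1 = 14. At the same noncentrality, power is 0.898 against 0.903.

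**The case against.** A reader might infer that randomisation is not stratified by company and that the company variance cannot be estimated, so that arm and company are likely to be confounded. The documents do not support this.

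- **Stratification.** The Randomization section is silent; it does not exclude stratification. A journal article may leave such detail to a fuller protocol. The steering groups at each company, and their task of shielding controls, make most sense if both arms sit inside each company. That is an indication, not a rule.
- **Estimability.** The variance can be estimated, only very imprecisely. That enterprise is random is the usual reading, not a stated fact.
- **Probabilities.** They rest on an unstated number of blocks. Simple allocation also fits poorly with the aim of at least 200 workers and 9 teams per arm.
- **Harm.** One company wholly in one arm is not full confounding, since the other two still give within-company contrasts. The analysis concerns change from T0 to T1, so stable company differences largely cancel. The type I errors in step 5 apply when the company term has dropped out; they are not the overall error rate of the planned model.
- **Remedy.** A fixed company effect without allocation within company could do harm: power about 0.52 under the unfavourable split.

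All of this stands and limits the point. It does not rescue a random level with three units, nor does it replace a stated allocation rule.

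**Conclusion.** The point holds in a limited form. Three enterprises are too few for a random level to be relied on: the SD interval spans about 0.5 to 6.3 times the estimate, and a zero estimate is common. This assumes that enterprise is random, as levels of a mixed model ordinarily are.

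The allocation risk is conditional. If blocks are not restricted by company, the chance of at least one company lying wholly in one arm ranges from 60% to 2.5% (balanced overall split) or 88% to 9% (simple allocation) for 2 to 6 blocks per company. The more damaging split, two companies in opposite arms, is less likely from 3 blocks upwards. What would then be mixed with the intervention effect is company-specific change in year one. If blocks are randomised evenly within company, the risk disappears and fixed versus random hardly matters. This is a cheap improvement to the plan, not an error that invalidates it.

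**What to change.** - **Randomization:** state that blocks are randomised within each company, as near 1:1 as possible.
- **Statistics:** enter company as a fixed effect, as the stratification factor, instead of a random level. Keep team and worker as random levels. In a repeated-measures model, let company act on the T0 to T1 change (company by time), since a company main effect alone adjusts only for stable differences.

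Make the two changes together; the second is safe only with the first. The cost is one short schedule per company, 2 degrees of freedom, and about half a point of power when arms are balanced within company. The allocation rule has to be set before randomisation. If blocks are already randomised within company, one sentence saying so settles that part.

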### Sample size calculation

The sample size was calculated based on the standardized effect size, a standardized difference between intervention and control groups. On the one hand, the PIPPI intervention is extensive, targeting a range of challenges in the work environment at various levels of the organization. On the other hand, the intervention is not equally intensive for every employee – the intensity depends on a number of circumstances, e.g. the number of action plans designed and completed in the work group, or whether the employee participates in the individual visual mapping session with his or her line manager. Thus on average, we assumed a medium effect size, corresponding to a standardized difference score of 0.50 [69].

Because we are not aware of any previous similar intervention study among manufacturing workers, we assume an intra-class correlation of .05 based on a previous cluster randomized controlled study on prevention of low back pain and its consequences among nurses’s aides in elderly care in Denmark [70]. With level of significance (α) of .05, a statistical power (1-β) of 0.9, intra-class correlation of .05, and a design effect of 1.54 (considering average cluster size of 22 workers), 200 (9 teams) workers in each group will be required.

Generally, workplace intervention studies have a high dropout rate. Also, there is a risk of organizational changes happening at workplace which can lead to drop-out of entire cluster from the evaluation. Therefore, we are aiming to randomize more than 400 workers (more than 18 teams) in both groups.

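### If the four listed model levels are fitted as nested random intercepts, team clustering drops out of the T0-to-T1 group-by-time test and the type I error may exceed 5%

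*Protocol article*

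**What the plan says.** The Statistics section describes a multi-level mixed model or generalized linear mixed model for the primary and secondary outcomes, "based on comparison between the intervention and the control group from baseline (T0) to 12 months after baseline (T1". On its structure it says: "Four levels will be included in the mixed model: time (measurement time points), worker, working team and enterprise". It then gives an assurance that the analyses "will concurrently take into account the clustering of observations of workers within the working team, as well as repeated measurements within each worker".

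The section does not say whether the random effects are intercepts only, and it neither includes nor excludes a team-by-time effect. Nor does it say whether the T0-to-T1 comparison is a group-by-time term with free baseline means or a T1 comparison adjusted for baseline.

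The only ICC in the article is in the Sample size calculation section: "we assume an intra-class correlation of .05 based on a previous cluster randomized controlled study". It is not described as an ICC of change.

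**The concern.** Listing time, worker, team and enterprise as levels is the ordinary way to describe occasions nested in workers, workers in teams and teams in enterprises. Its default fit has one random intercept per worker, per team and per enterprise. A team intercept absorbs a team's stable level. It does not absorb a team's own movement between T0 and T1, and that movement is what adds noise to a comparison of changes between groups of teams.

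An analyst could therefore follow the Statistics section to the letter and test a cluster-randomised trial as if workers had been randomised individually. Both primary outcomes, and any secondary outcome analysed this way, would have standard errors that are too small. A difference due to ordinary team-level drift could be read as an intervention effect.

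The article gives reasons to expect such drift in either arm. The Sample size calculation section foresees organisational changes severe enough to lose entire clusters. Limitations and risks foresees control groups starting activities of their own.

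**Working it through.** **Inputs.** From the Sample size calculation section: 22 workers per team, 9 teams per arm, ICC .05 and α .05 (sidedness not stated; two-sided assumed). Not in the article and therefore assumed: the ICC of the T0-to-T1 change, ρ, varied from 0 to .05.

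**The plan's own figure.** The article states "intra-class correlation of .05, and a design effect of 1.54 (considering average cluster size of 22 workers". The usual formula gives 1 + (22 − 1) × .05 = 2.05, not 1.54. For an effect of 0.50 SD at 90% power, 85 workers per arm are needed before inflation. Then 85 × 1.54 = 130.9 and 85 × 2.05 = 174.25, so neither product gives the stated 200. That mismatch is a separate matter. The article states no type I error for the mixed model other than the nominal .05.

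**Step 1: cancellation.** With intercepts only, the outcome of worker i in team j at time t is

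y = fixed effects + enterprise + team(j) + worker(i) + e(ijt).

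Subtracting T0 from T1 removes enterprise, team and worker. What remains is the time and group-by-time effects plus e(ij1) − e(ij0), which the model treats as independent between workers of the same team. With balanced data the test is then the ordinary two-sample t test on individual changes. I checked this by fitting the random-intercept model to three simulated datasets (18 teams of 22). The group-by-time statistic and the t statistic on changes agreed to at least five decimals each time, for example 1.46243 from both.

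**Step 2: size of the error.** If changes within a team correlate by ρ, the true variance of the contrast is larger than the model's by D = 1 + 21ρ. The standard error is too small by √D, and the type I error is 2 × [1 − Φ(1.96/√D)].

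| ρ (assumed) | D | √D | Type I error |
|---|---|---|---|
| 0 | 1.00 | 1.00 | 5.0% |
| .01 | 1.21 | 1.10 | 7.5% |
| .02 | 1.42 | 1.19 | 10.0% |
| .05 | 2.05 | 1.43 | 17.1% |

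**Step 3: simulation.** I ran 20,000 null datasets per setting with 9 teams of 22 per arm. The worker-level test rejected in 4.8% at ρ = 0, 10.1% at .02 and 17.3% at .05. A t test on team-mean changes with 18 − 2 = 16 degrees of freedom rejected in 4.8-5.2% in every setting.

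**Step 4: which ρ is credible?** Suppose the stated .05 is the ICC at a single occasion. Let c be the correlation over the year of the team effects and w that of the worker-level deviations (both assumed). Then

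ρ = .05(1 − c) / [.05(1 − c) + .95(1 − w)].

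- c = 1: ρ = 0, type I error 5%.
- c = 0.9, w = 0.6: .005/(.005 + .38) = .013, 8.2%.
- c = 0.8, w = 0.6: .010/(.010 + .38) = .026, 11.4%.
- c = 0.5, w = 0.5: .025/(.025 + .475) = .05, 17.1%.

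The result depends mainly on how stable team means are over the year, on which the article gives no figure.

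**The case against.** The strongest reply is that the article never says intercepts only. It states outright that team clustering will be handled, and a team-by-time effect would be consistent with its wording. So would a T1 comparison adjusted for baseline with a team effect, which is one of the remedies proposed here. The covariance structure is commonly left to the statistical analysis plan, which is not shown. This stands, and it makes the point conditional. It does not remove it: the article names both the levels and the contrast and offers the levels as the answer to clustering, and for that contrast their default reading does not deliver.

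Two stronger inferences are tempting and are not supported.

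- **That the planned test has a false-positive rate of some 8-17%.** That range holds only for an ICC of change of about .0125 to .05, which the article does not give. The rate is 5% at zero, and above 17% if team means are less stable. The stated .05 cannot simply be taken as an ICC of change.
- **That differing action plans and intensity between teams prove the inflation.** That is variation of the treatment effect in the intervention arm. If the intervention does nothing in any team, it adds no team-specific change. Type I error is inflated by background drift, for which the organisational changes and the control groups' own activities are the relevant evidence. The article quantifies neither.

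The cancellation is exact for a linear model with balanced data. With missing follow-up or a non-linear link it need not be exact.

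**Conclusion.** The point holds conditionally. Under the ordinary nested-intercept reading of the Statistics section, with the effect tested as group-by-time, the team and enterprise levels do not protect the T0-to-T1 contrast, contrary to the stated assurance. With 22 workers per team the type I error is then 7.5%, 10.0% or 17.1% at assumed ICCs of change of .01, .02 or .05, and 5% only if teams do not drift apart at all. The mechanism is certain under that reading. Whether the sponsor intends that reading, and how large the ICC of change is, cannot be settled from the article. A reader should not conclude that the trial's analysis is invalid, only that the text permits an invalid one and should be closed off.

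**What to change.** State the random-effects structure for the primary contrast, in one of two forms:

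1. Keep the T0/T1 repeated-measures model and add a random cluster-by-time effect: team-by-time, and likewise block-by-time, because the Randomization section allocates blocks of teams and the block is not among the four listed levels.
2. Analyse the T1 value with the worker's T0 value as covariate and a random cluster intercept. Clustering then stays in the standard error.

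In either form, refer the effect to a t distribution with degrees of freedom based on the number of clusters (Kenward-Roger or Satterthwaite). An analysis of cluster-mean changes is a simple check.

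The cost is a sentence of model specification and no new data. Relative to the intercept-only group-by-time model, confidence intervals widen by about 10-40% if the ICC of change is .01-.05 (√1.21 = 1.10 to √2.05 = 1.43). The cluster-based t quantile adds a little more. If the sponsor already intends one of these forms, saying so settles the point.

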### Sample size calculation

The sample size was calculated based on the standardized effect size, a standardized difference between intervention and control groups. On the one hand, the PIPPI intervention is extensive, targeting a range of challenges in the work environment at various levels of the organization. On the other hand, the intervention is not equally intensive for every employee – the intensity depends on a number of circumstances, e.g. the number of action plans designed and completed in the work group, or whether the employee participates in the individual visual mapping session with his or her line manager. Thus on average, we assumed a medium effect size, corresponding to a standardized difference score of 0.50 [69].

Because we are not aware of any previous similar intervention study among manufacturing workers, we assume an intra-class correlation of .05 based on a previous cluster randomized controlled study on prevention of low back pain and its consequences among nurses’s aides in elderly care in Denmark [70]. With level of significance (α) of .05, a statistical power (1-β) of 0.9, intra-class correlation of .05, and a design effect of 1.54 (considering average cluster size of 22 workers), 200 (9 teams) workers in each group will be required.

Generally, workplace intervention studies have a high dropout rate. Also, there is a risk of organizational changes happening at workplace which can lead to drop-out of entire cluster from the evaluation. Therefore, we are aiming to randomize more than 400 workers (more than 18 teams) in both groups.

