### Study population

This study aims to recruit larger industrial workplaces in Denmark employing workers organized in teams mainly carrying out manufacturing work.

The inclusion criteria at the *workplace level* is that the workplace should (a) have at least 100 employees mainly involved in manual labor work, (b) be team based, (c) have a fairly cooperative relation between different levels of organization, (d) be willing to implement the PIPPI activities and (e) reflect the geographical and organizational distribution of Danish industrial production companies. Inclusion criteria at the *team level* are that the employees are organized in teams of formal work groups. Inclusion criteria at the *individual level* are that the participants should (a) work for ≥20 hours/week and (b) give consent to participate in the scientific evaluation of the study. PIPPI is an organizational-level intervention and all workers in the intervention group will participate in intervention activities. Thus, there are no individual exclusion criteria for participating in the intervention activities. However, only the workers who satisfy the individual level criteria will be included in the effect evaluation of this study.

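### The recruitment target offered as protection against dropout and lost clusters starts at the number already called required, so it holds no quantified allowance, and the power left after attrition cannot be read from the plan

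*Protocol article*

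**What the plan says.** The Sample size calculation section of the protocol article ends its derivation with "200 (9 teams) workers in each group will be required". The next paragraph opens with "Generally, workplace intervention studies have a high dropout rate". It adds that organizational change may remove an entire cluster from the evaluation, and then draws its conclusion: "Therefore, we are aiming to randomize more than 400 workers (more than 18 teams) in both groups".

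The abstract (Methods/Design) shows that 400 is the total over the two groups. It aims for more than 400 workers, with "at least 200 workers (at least 9 work teams) in each group".

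The Study population section adds that "only the workers who satisfy the individual level criteria will be included in the effect evaluation of this study". Those criteria are working at least 20 hours a week and consenting to the scientific evaluation.

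**The concern.** The attrition paragraph exists to justify a margin above the calculated requirement. The only firm number it yields is the requirement itself, with an unspecified amount on top. A trial that randomized 401 workers in 19 teams would meet the target, and almost any dropout would then leave fewer than the 200 per group called necessary.

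The stated 0.90 therefore describes a trial with complete follow-up, which the authors say they do not expect. Losing whole teams matters most. With about 9 teams per arm, each lost team removes both information and degrees of freedom, and the plan itself names that loss as a risk.

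The reader cannot judge how much is at stake, because no dropout rate or cluster loss is given and the printed design effect does not follow from its own inputs.

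**Working it through.** **Inputs, all from Sample size calculation.** Standardized difference: "corresponding to a standardized difference score of 0.50". Significance: "With level of significance (α) of .05", taken as two-sided because the section does not say. Power: "a statistical power (1-β) of 0.9". Intra-class correlation (ICC) .05, average cluster size 22, printed design effect 1.54, 9 teams per group.

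**Target against requirement.** 2 x 200 = 400 workers and 2 x 9 = 18 teams. The target is above 400 and above 18, so its guaranteed margin is unstated.

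**Reproducing 200 per group.** Without clustering, n = 2(1.960 + 1.282)²/0.50² = 84.1, so 85 per group.

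- With the printed design effect: 85 x 1.54 = 130.9, so 131 per group (about 6 teams).
- With the design effect that ICC and cluster size imply: 1 + (22 - 1) x .05 = 2.05, and 85 x 2.05 = 174.3, so 175 per group (about 8 teams).

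Neither gives 200. A design effect of 1.54 would need a cluster size of 1 + .54/.05 = 11.8, or an ICC of .54/21 = .026. Of the variants tried, the one that supports 9 teams at 0.90 uses 2.05 with a t test on team-level degrees of freedom, 2(k - 1) = 16. It gives 0.903 at 9 teams of 22 and 0.861 at 8.

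**Power after attrition.** No dropout rate is given, so 20% and 30% are assumptions. For k teams per arm and dropout d: m = 22(1 - d); design effect = 1 + (m - 1) x .05; effective n per arm = km / design effect; noncentrality = 0.50 x √(effective n / 2).

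| Teams per arm | Dropout | m | Design effect | Effective n | Power, t on 2(k - 1) df | Power, normal |
|---|---|---|---|---|---|---|
| 9 | 0% | 22.0 | 2.05 | 96.6 | 0.903 | 0.935 |
| 9 | 20% | 17.6 | 1.83 | 86.6 | 0.870 | 0.908 |
| 9 | 30% | 15.4 | 1.72 | 80.6 | 0.846 | 0.888 |
| 8 | 0% | 22.0 | 2.05 | 85.9 | 0.861 | 0.906 |
| 8 | 20% | 17.6 | 1.83 | 76.9 | 0.822 | 0.873 |
| 8 | 30% | 15.4 | 1.72 | 71.6 | 0.795 | 0.849 |

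**Where 0.90 is crossed, with all 9 teams kept.** About 3% dropout on the t basis, about 25% on the normal basis with the design effect recomputed, and about 34% if 1.54 is taken at face value.

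**What a stated allowance would look like.** If 200 per group are needed at analysis, 200/(1 - 0.20) = 250 and 200/(1 - 0.30) = 286 per group would be randomized, or 500 and 572 in total. These figures only show scale.

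**The case against.** A reader might infer that the target equals the requirement, so that the margin is zero. The text does not say that. Both the section and the abstract use open-ended floors, so the margin is unspecified, and only the absence of a quantified allowance can be held against the plan.

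A reader might also infer that 0.90 power is lost. That does not follow from the printed inputs. Taken as printed, they need only 131 per group, and 200 would then absorb about 34% dropout. With 2.05 and a normal approximation, 0.90 still holds at 20% dropout with all teams kept. This part of the objection stands, and the conclusion must be conditional. The slack at 1.54 is weak support, however: it comes from a design effect that contradicts the section's own inputs, and the section nowhere presents 200 as already inflated. The t basis is not stated in the plan either, although it is the appropriate one with 9 clusters per arm.

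It is also tempting to say that the consent and hours criteria cut the numbers further. The documents do not show this. Consent is collected during recruitment, and the 400 may already be eligible, consenting workers. This is an ambiguity about what is being counted.

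Finally, the Statistics section plans a multi-level repeated-measures model using baseline, with missing-data sensitivity analyses, which would tend to raise power above these two-group figures. The amount cannot be computed without the correlation between time points. In the other direction, the Randomization section allocates blocks of teams, so the independent units may number fewer than 18. The number of blocks is not given.

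**Conclusion.** The point holds in a limited form. The target put forward as the answer to dropout and cluster loss contains no stated allowance, because it starts at exactly the number required. That conclusion rests on the text alone.

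The effect on power is conditional on assumed dropout, an ICC of .05, 22 workers per team, a two-sided 5% test and equal loss in both arms. At 20-30% dropout, power is 0.87-0.85 on the t basis or 0.91-0.89 on the normal basis. With one team per arm also gone, it is 0.82-0.79 or 0.87-0.85. These are modest losses and do not undermine the trial. The unqualified 0.90 should still not stand beside a warning of high attrition and a design effect that does not reconcile with its inputs.

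**What to change.** In Sample size calculation:

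1. Correct the design effect, or correct the ICC or cluster size behind it, so that the three agree.
2. Say whether 200 per group means evaluable workers (consenting, at least 20 hours a week) at the 12-month follow-up. If 200 already includes a reserve, say so.
3. State the assumed worker dropout and the assumed number of lost clusters.
4. Replace the unqualified 0.90 with the power left at 400 workers in 18 teams under those assumptions, naming the basis. A t reference with cluster-level degrees of freedom is preferable with 9 clusters per arm.

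In addition, where contact is possible, send the 12-month questionnaire to consenting workers whose team has been reorganised, and analyse them in the block as randomised. This acts directly on the cluster loss that the plan fears.

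The cost is a few sentences, probably a less favourable power figure, and modest follow-up effort. Some workers will have left the workplace and cannot be reached. No extra recruitment is needed to make these changes.
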